### Safety aspects

The NeuroSIRS-Study will be conducted at the Phase I, Clinical Study Core Unit at the University Hospital of Bonn, Germany. Here, participants will be connected to a monitoring system, measuring heart rate (electrocardiogram, ECG), blood pressure (in intervals, non-invasively), oxygenation and respiratory rate continuously for 3.5 h. Body temperature will be taken upon arrival and after lying down for 15 min. For analysis of heart rate variability as a marker for sufficient VNS, ECG will be taken until dismissal from the Phase I unit.

Safety of taVNS during systemic inflammation will be assessed based on the rate of AEs, SAEs, ADEs, and SADEs.

### Statistical analysis

The analysis of the study data will be descriptive. Differences for primary and secondary outcome parameters between the treatment groups will be estimated with 95% confidence limits. The evaluation of the effectiveness parameters will be performed with all randomized subjects first and in addition for the subjects who were compliant to the protocol. The evaluation of the safety parameters is carried out with all subjects on whom one of the study procedures was carried out in whole or in part.

Study participants who withdraw from the study prematurely before the second application of SmartPill® will be replaced by additional study participants. Likewise, study participants who have a malfunction of the SmartPill® will be replaced. The probability of a malfunction of the capsule is estimated by the distributing company to be less than 5%.

All test persons who leave the study prematurely will be listed and monitored. A follow-up is not necessary. The reason for their withdrawal is documented. The data available up to the time of withdrawal are included in the evaluation. Individual missing values are not replaced for the evaluation.

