## Methods and analysis

### Sample size, recruitment, and blinding

The NeuroSIRS-Study is a prospective, randomized, two-armed, sham-controlled, double-blind, exploratory clinical trial in healthy subjects. It is a pilot study with the intention to gain first insights into the primary and secondary objectives. Therefore, sample size is not based on a statistical rationale. Thirty participants will be enrolled in the study: 15 subjects in the experimental group and 15 subjects in the control group. Healthy volunteers will be recruited by advertisements placed at the University Hospital of Bonn and in the local newspaper. During the screening visit, potential participants will be informed about the NeuroSIRS-Study. After sufficient time for consideration, a written informed consent will be obtained. Participants failing to meet inclusion criteria will not be enrolled in the study.

Since the NeuroSIRS-Study is an exploratory trial designed to give first insight into the impact on taVNS during systemic inflammation and to achieve the best possible comparability, it was decided to include only Caucasian men into the study. To ensure equal distribution of known and unknown variables between both groups, a randomization will be carried out upon enrolment. Patients are randomized to one of two therapy arms (arm A: taVNS application; arm B: sham stimulation/control). Randomization will be performed using central fax randomization according to a randomization list supplied by the Institute of Medical Biometrics, Informatics and Epidemiology, Study Center, University Hospital of Bonn. Participants and study personnel will be blinded until completion of the NeuroSIRS-Study. Application of the taVNS device will be carried out by study personnel. Stimulation settings (electrical stimulation or sham, i.e., no stimulation) will be adjusted by an independent physician who is otherwise not involved in the study. The stimulation settings will be concealed without the possibility for the investigator or the participant to see the settings.

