#### Secondary objectives

Evaluation whether taVNS can influence gastrointestinal motility during SIRS by comparison of intestinal pH, intraluminal pressure, and peristaltic activity between both groups. Intestinal barrier function will be compared using the lactulose/mannitol ratio between the two arms.Change of activity of the autonomous nerve system is investigated during and after taVNS or sham stimulation via heart rate, blood pressure, and heart rate variability.Safety of taVNS after LPS application is evaluated based on the rate of adverse events (AEs), serious AEs, adverse device-related events (ADEs), and serious ADEs.Affection of the immune system by comparison of the plasma concentration of pro- and anti-inflammatory cytokines such as TNF-α, IL 6, IL 8, IL 10, IL 18, IL 1β, and HMGB-1 as well as immune cells before and after taVNS or sham stimulation.

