### Intervention

After completed screening (medical history, physical examination with ECG, blood pressure, O2 saturation, and blood tests), participants ingest the SmartPill® and leave the hospital. The capsule analyzes peristaltic activity as well as gastric emptying time, small bowel transit, large bowel transit, and whole gut transit in the absence of an inflammatory stimulus. Those measurements serve as an intraindividual reference, as transit time and motility vary between individuals. After 5 days, subjects return to the phase I unit of the hospital to proceed with the trial. Upon confirmation of excretion of the capsule, another SmartPill® is ingested.

Subjects are randomized and either undergo taVNS or sham stimulation for 30 min before LPS application. LPS is administered at 2 ng/kg bodyweight to all subjects. One hour after administration, taVNS is terminated. ECG and SpO2 are measured continuously for 3.5 h, starting just before stimulation. Blood pressure, body temperature, and respiratory rate are measured every half hour for 3 h. Until discharge of the participant, vital signs are measured hourly.

LPS‐induced flu‐like symptoms (headache, nausea, shivering, muscle, and back pain) are scored per symptom (0 = no symptoms, 5 = worst ever experienced, vomiting: additional 3 points resulting in a total symptom score of 0–28) before taVNS and at 1 h, 1.5 h, 2 h, 2.5 h, 3 h, 3.5 h, 4 h, 5 h, 6 h, and 7 h after the beginning of taVNS as suggested by Kox et al. [37–40].

During screening; before taVNS; before starting of LPS administration; at 1 h, 1,5 h, 2 h, 2.5 h, 3 h, 4 h, 6 h, and 7 h after the beginning of taVNS; and at the final examination blood samples are drawn and analyzed for pro- and anti-inflammatory parameters (TNF-α, IL 6, IL 8, IL 10, IL 18, IL 1β, HMGB-1) and changes in blood cell count.

Subjects leave the hospital and return after 5 days to confirm capsule excretion and for final clinical examination (Table 1).

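### The first SmartPill is collected as a within-person reference, but the motility objective and the analysis section do not carry it into the group comparison; ANCOVA on the first-capsule value would

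*Protocol article*

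**What the plan says.** The Intervention section of the protocol article has each participant swallow one SmartPill after screening, to measure transit and peristaltic activity without an inflammatory stimulus. It gives the reason: "Those measurements serve as an intraindividual reference, as transit time and motility vary between individuals". The participant returns after five days, and then: "Upon confirmation of excretion of the capsule, another SmartPill® is ingested". This second capsule covers the stimulation and the LPS challenge.

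The Secondary objectives section frames the motility question as "comparison of intestinal pH, intraluminal pressure, and peristaltic activity between both groups" and does not mention the first capsule. The same section words other outcomes differently: autonomic activity as a change during and after stimulation, and cytokines as a comparison before and after stimulation.

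The Statistical analysis section calls the analysis descriptive and adds: "Differences for primary and secondary outcome parameters between the treatment groups will be estimated with 95% confidence limits". It names no covariate, change score or within-person contrast.

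On size: "Thirty participants will be enrolled in the study: 15 subjects in the experimental group and 15 subjects in the control group". The article also says: "Therefore, sample size is not based on a statistical rationale".

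**The concern.** The article identifies between-person variation as the problem and asks participants for an extra capsule and a five-day interval to deal with it. It then states the objective and the estimate in a form that leaves this variation in the error term, unless something further is done. Three analyses fit the text: a raw difference between arms on the second capsule, a difference in change from the first capsule, and a difference adjusted for the first capsule. Their precision differs materially.

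The trial tests no hypothesis to a power target, so its interval estimates are its main product and are meant to inform later trials. With 15 per arm those intervals are wide, and chance differences at baseline are quite possible. Fixing the contrast before unblinding also removes the option of choosing among three analyses after seeing the results.

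**Working it through.** The article states no SD, effect size or power, so there is no figure of its own to reproduce. The check compares the precision of the three candidate analyses.

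**Inputs**
- 15 per arm (section Sample size, recruitment, and blinding).
- 95% confidence limits, taken as two-sided (section Statistical analysis).
- r, the correlation between first- and second-capsule values. The article does not give it, so it is assumed and varied. The first capsule is taken without LPS and the second with it, which could lower r.
- Equal SD on both capsules, assumed. This matters for the change score.

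**Formulas, half-width in units of the outcome SD**
- Unadjusted: t(0.975; 28) × √(2/15) = 2.048 × 0.365 = 0.748.
- ANCOVA: t(0.975; 27) × √[(2/15) × (1 − r²) × 27/26], with t = 2.052. The factor 27/26 is the average price of estimating the covariate slope in 30 people.
- Change score: t(0.975; 28) × √[(2/15) × 2(1 − r)].

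Example for ANCOVA at r = 0.5: 2.052 × √(0.1333 × 0.75 × 1.0385) = 2.052 × 0.322 = 0.661.

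| r | Unadjusted | ANCOVA | ANCOVA relative to unadjusted | Change score |
|---|---|---|---|---|
| 0 | 0.748 | 0.763 | 2% wider | 1.058 |
| 0.2 | 0.748 | 0.748 | equal | 0.946 |
| 0.3 | 0.748 | 0.728 | 3% narrower | 0.885 |
| 0.5 | 0.748 | 0.661 | 12% narrower | 0.748 |
| 0.7 | 0.748 | 0.545 | 27% narrower | 0.579 |

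A simulation with 5,000 runs at each of r = 0.3, 0.5 and 0.7 gave ANCOVA-to-unadjusted width ratios of 0.97, 0.88 and 0.73, in agreement with the formula.

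**In terms of sample size.** Ignoring small-sample terms, ANCOVA is worth 15/(1 − r²) per arm in an unadjusted comparison: 16.5 at r = 0.3, 20 at 0.5 and 29.4 at 0.7.

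**Chance imbalance.** The difference between two baseline means has a standard error of √(2/15) = 0.365 SD. By normal approximation it exceeds 0.25 SD in either direction with probability about 49%, and 0.5 SD with probability about 17%.

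**Which baselines exist**
- SmartPill measures: the first capsule, which precedes any stimulation.
- Heart rate and heart rate variability: the ECG starts just before stimulation.
- Cytokines: blood is drawn before taVNS and again before LPS. Stimulation starts 30 min before LPS, so the second of these samples already follows treatment and is not a baseline.
- Lactulose/mannitol: the test is described only for the period of LPS challenge and taVNS, with no baseline test.
- Symptom score: scored before taVNS, but healthy volunteers should be near 0 then, so there is little for the covariate to explain.

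**The case against.** A reader might infer that the plan discards the first capsule and commits to an unadjusted analysis. The article does not support this. It assigns the first capsule a use, and its sentence on group differences would equally cover a difference in change or an adjusted difference. Nothing rules out adjustment. For autonomic activity and cytokines the objectives already refer to change or to before and after, so for those outcomes the question is which baseline method to use, not whether the baseline is ignored. This part of the objection stands.

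It can also be said that a journal article leaves the model to a fuller protocol or an analysis plan, neither of which is shown. That is fair, and if such a document names the model, the point is met. What remains is more than silence about a model: the article justifies an extra procedure by between-person variation, and then words both the objective and the estimate without it.

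Two further limits stand. The unadjusted randomised comparison is unbiased, in a trial that describes itself as an exploratory pilot. And a reader might think adjustment is free, or that it helps every outcome. It is slightly harmful below r of about 0.2, it cannot be applied to lactulose/mannitol as described, and it adds little for the symptom score, which bears on the primary objective.

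**Conclusion.** The point holds as a matter of precision for secondary outcomes. The article gives a reason for collecting the first capsule but does not connect it to the stated motility comparison.

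Under the assumed correlations, adjustment narrows the intervals by about 3% at r = 0.3, 12% at 0.5 and 27% at 0.7. The possible loss is about 2% if the capsules are uncorrelated. A raw change score is the less safe way to use the reference: below r = 0.5 it is less precise than no adjustment. The size of the gain rests wholly on r, which the article does not report. The direction of the recommendation does not depend on its exact value, provided r is above about 0.2.

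The conclusion does not extend to a claim of bias, or to a claim that baseline data are thrown away.

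**What to change.** Add to the Statistical analysis section wording such as: *For each SmartPill measure, the difference between groups in the second-capsule value will be estimated with 95% confidence limits by ANCOVA, adjusted for the same participant's first-capsule value. Heart rate, blood pressure and heart rate variability will be adjusted in the same way for the value before stimulation. Where cytokines are adjusted, the baseline will be the sample taken before taVNS.*

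Name the blood-pressure reading that serves as baseline, because the Intervention text does not say whether the half-hourly series begins before stimulation. Do not extend the rule to lactulose/mannitol.

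The cost is a short addition to the text, one degree of freedom (critical t from 2.048 to 2.052), and up to about 2% in interval width if the baseline proves uninformative. A participant without a readable value on either capsule drops out of that adjusted comparison, since the article does not replace missing values. This is most likely for small- and large-bowel transit, where the Limitations section expects difficulty in reading the ileocaecal passage. No new data or visits are needed.

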### Exclusion criteria

Age < 18 years; > 45 years; female sex; active smoker; constipation or diarrhea; surgical procedures or trauma-necessitating blood transfusion; donation of blood within the past 4 weeks; immunosuppressive or immunomodulatory medication in the past 6 months; medication with known influence on cholinergic, dopaminergic, adrenergic, or serotoninergic neurotransmission; history of cardiovascular disease or vasovagal/orthostatic syncope in the past 12 months; heart rate < 45/min or > 110/min; systolic blood pressure > 160 or < 90 mmHg; known polarization and repolarization disturbances; obstructive pulmonary disease or allergic asthma; pacemaker or internal defibrillator or any other electrical implant; seizures; impaired kidney function with serum creatinine above average; alkaline phosphatase or aspartate transaminase three times higher than normal; immunosuppression (hereditary, acquired, or drug induced); c-reactive protein above average and/or leukocytosis above average or current infection; infection within past 2 weeks before study; known allergy or hypersensitivity to one of the components of the medical device; conditions or diseases which do not fit with the study at the investigator’s discretion; known dysphagia; non-steroidal anti-inflammatory drug enteropathy in the past; patients with cerebral shunts; patients with active implantable devices, medication with proton pump inhibitors (PPIs), antacids, or H2 blockers; reflux esophagitis grade III and IV according to Savary and Miller; fistulas of the esophagus and/or stomach; known or suspected stenoses or fistulas of the GI tract; active Crohn’s disease; diverticulosis or diverticulitis; any abdominal surgery in the past 3 months; history of abdominal surgery (excluded: appendectomy, cholecystectomy, or any minimally invasive performed surgery); type I diabetes; diseases of the adrenal glands; splenectomy; prior participation at a study with LPS application; incapacity to fully understand the study; known misuse of alcohol, medication, or drugs in the past; former participation in LPS challenge.

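### The waiver of follow-up for early leavers also covers men who have already swallowed a capsule or received stimulation, sham or LPS

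*Protocol article*

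**What the plan says.** The rules for early leavers are in the last paragraph of Statistical analysis in the protocol article. Leavers are first mentioned with "All test persons who leave the study prematurely will be listed and monitored", and the next sentence is "A follow-up is not necessary". What monitoring consists of, and for how long, is not stated. On the data, the rule is "The data available up to the time of withdrawal are included in the evaluation". The safety evaluation covers "all subjects on whom one of the study procedures was carried out in whole or in part", so anyone who has begun a procedure stays in the safety set.

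The Intervention section describes two capsules.

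- **First capsule.** After screening, "participants ingest the SmartPill® and leave the hospital". The check comes at the return visit after 5 days: "Upon confirmation of excretion of the capsule, another SmartPill® is ingested".
- **Second capsule.** It is swallowed at that return visit, before stimulation or sham and LPS. The check comes at the last visit: "Subjects leave the hospital and return after 5 days to confirm capsule excretion and for final clinical examination".

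Secondary objectives and Safety aspects both name the rates of AEs, SAEs, ADEs and SADEs as the safety outcome. The section on data collection and safety management refers to adverse-event documentation under ICH-GCP and ISO 14155 after enrolment, and to a separate safety management plan.

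**The concern.** One rule is applied to all leavers, whether they have received nothing, a capsule, stimulation or sham, or LPS. For a man who has received nothing, waiving follow-up is harmless. For an exposed man it removes the only scheduled points at which capsule transit, late adverse events and clinical state would be checked.

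Two things are at stake.

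1. **Participant safety.** A 26 × 13 mm capsule may be left with no requirement to confirm that it has passed. The exclusion of men with "known or suspected stenoses or fistulas of the GI tract" suggests that capsule transit is a recognised concern, although the article does not give the reason, so this is an inference. The second capsule is swallowed on the day of the LPS challenge, and the Discussion expects that challenge to impair gut motility.
2. **The safety objective.** An exposed leaver counts in the denominator of every adverse-event rate, while events after he leaves may not be recorded. Leaving may also be related to tolerability, since the Discussion expects potent symptoms and possible discomfort from LPS.

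**Working it through.** The plan gives no figure on this point to reproduce. The check has two parts: what is observed for each exposure, and how much an unobserved leaver could shift a rate.

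**Observation windows (from Intervention)**

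| Exposure | Scheduled observation on the unit afterwards | Next excretion check |
|---|---|---|
| First capsule | None; the man goes home | After 5 days = 5 × 24 = 120 h |
| Second capsule | To at least 7 h after taVNS starts (last symptom score and on-unit sample) | 5 days (120 h) after leaving the unit |
| LPS | Given 0.5 h after taVNS starts, so 7 − 0.5 = 6.5 h | Not applicable |

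The article gives no discharge time, so 7 h is a minimum. The Discussion puts full reversal of LPS symptoms at 6–8 h. Most of the acute LPS risk is therefore seen on the unit, and the gap concerns mainly the capsule and later events.

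**Effect on adverse-event rates**

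Inputs: 15 men per arm (Sample size, recruitment, and blinding). *Assumption:* 0 to 2 randomised, exposed leavers in one arm, because no withdrawal rate is given. The calculation is meant for rare categories (SAE, ADE, SADE).

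With no events, the exact two-sided 95% upper limit is 1 − 0.025^(1/n):

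- as reported, 0/15: 1 − 0.025^(1/15) = 21.8%
- fully observed men with one leaver, 0/14: 1 − 0.025^(1/14) = 23.2%
- fully observed men with two leavers, 0/13: 1 − 0.025^(1/13) = 24.7%

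The reported limit is thus too low by 23.2 − 21.8 = 1.4 points or 24.7 − 21.8 = 2.9 points. With no leavers there is no effect.

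If each leaver had an event that nobody saw, the report would still read 0/15. The true figures, with Clopper-Pearson upper limits and Newcombe limits for the difference from 0/15 in the other arm, would be:

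| True count | Rate | Exact 95% upper limit | Difference from 0/15 | Newcombe 95% limits |
|---|---|---|---|---|
| 1/15 | 6.7% | 31.9% | 6.7 points | −14.4 to 29.8 |
| 2/15 | 13.3% | 40.5% | 13.3 points | −9.2 to 37.9 |

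In the order given under Intervention, a man who leaves after the first capsule is not yet randomised. He is in the safety set but in neither arm, so for him the issue is safety and not the comparison.

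**The case against.** The strongest reply is that the sentence stands in a statistical section, straight after a statement that leavers are monitored. It could mean only that no outcome follow-up is needed for the evaluation. Safety conduct is described elsewhere, under ICH-GCP and ISO 14155, with no stated cut-off at withdrawal and with a safety management plan that is not shown. Saying that follow-up is unnecessary does not forbid it.

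There are also mitigating facts. The receiver records the temperature drop at excretion, so excretion could be read from it if it is returned. The men are healthy and screened for GI disease. The group reports an earlier trial showing the capsule to be safe in abdominal surgery patients. LPS symptoms are short-lived. The trial is a descriptive pilot of 30, and the shift in limits without unseen events is small.

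Much of this stands. The problem is a risk, not something shown to occur; the plan that is not shown may cover part of it; and the statistical effect is minor unless leavers have unseen events. But nothing in the article requires an excretion check or an adverse-event contact after withdrawal. Monitoring is left undefined and sits uneasily beside the sentence that follows it. Return of the receiver is not described for leavers. Nor is this a detail that a condensed article simply leaves out: it is an explicit rule, drawn too broadly. If the safety management plan does require follow-up of exposed leavers, the article's wording still reads differently and needs a cross-reference.

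**Conclusion.** The concern holds. Read as written, the rule lets a man leave with a capsule whose excretion nobody is required to confirm, for either capsule, and lets later adverse events go unrecorded for men who stay in the safety set. Participant safety is the main reason to change it.

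The statistical consequence is limited. It is nil with no leavers, and 1.4 to 2.9 points on an upper confidence limit with one or two leavers and no events. It reaches 6.7 to 13.3 points on an arm's rate only if those leavers had unseen events. These sizes rest on an assumed 0 to 2 exposed leavers in one arm. Confidence is medium because the safety management plan is not available. The change is a cheap improvement that should be made.

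**What to change.** Replace the sentence that waives follow-up with wording such as: *Participants who leave before swallowing any SmartPill and before stimulation, sham or LPS need no follow-up. Anyone who leaves after any of these is followed for adverse events and, where a capsule's excretion is unconfirmed, for its excretion, at the scheduled 5-day visit or by telephone, unless he withdraws consent to further contact or data collection.* Define *monitored* to match, or refer to the safety management plan if it already provides this.

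The cost is two sentences in the protocol and one visit or call for each exposed leaver. It cannot recover a man who refuses contact or does not respond.
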